### Data analysis

Analyses will follow an intent-to-treat strategy comparing patients in the groups to which they were originally randomized.

All data will be scored and rescored by separate staff members and checked for accuracy prior to double entry into a REDCap database. Before conducting inferential statistics, we will explore data using descriptive analyses, data visualization, and examining the distributions of all imaging and clinical data. When necessary for continuous variables used as dependent variables, appropriate transformations to obtain approximate normality will be performed.

We will test a priori Primary Hypotheses in the 60 depressed participants by assessing a treatment-by-time interaction in multiple general linear models with repeated measures analyses in an intent-to-treat analysis applied to our various brain measures as dependent variables, including cortical thickness, task-based fMRI activation, resting state connectivity, and FA & ADC measures. Treatment (high vs low frequency) will be the independent variable. When testing hypotheses, we will account appropriately for the correlation of repeated measures across the two time points of measurement (baseline and 1 year) and the spatial correlation within each of our imaging measures. Covariates will include age and sex of the participants. We will examine parameter estimates and 95% confidence intervals, approximate the p-values of component terms, and estimate effect sizes in our final models. Least squares estimates (or maximum likelihood estimates) and their standard errors will be calculated for all models and plotted to assist in interpretation of significant main effects and their interactions. We will ensure that overall, study-wide Type I error-rate is maintained, correcting for multiple comparisons using False Discovery Rate (FDR). FDR-corrected *p*-values < 0.05 will be color-coded and displayed on a template brain.

The 30 healthy controls will be used to estimate the mean and variance of brain measures in the healthy population quantify the effects of high and low frequency psychoanalysis on brain measures and to aid their interpretation as either normalizing a previously abnormal brain measure or introducing a new brain difference that attenuates symptoms.

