The prototypical study design in modern medicine for inferring causation is the Randomized Controlled Trial (RCT), which assesses the effects of an experimentally manipulated intervention on the dependent (outcome) variable, usually illness severity. RCTs studying the efficacy and effectiveness of psychotherapy traditionally use clinical measures of symptom change as their primary outcome measure. Many cognitive, behavioral, and neural systems influence symptom severity, however, making these outcome measures very noisy, which in turn reduces the statistical power to detect real change that the therapies produce. Low statistical power in turn necessitates large numbers of participants to detect significant effects of the intervention, thereby increasing the size, duration, and cost of RCTs. Instead of employing change in symptom severity as the usual clinical outcome measure, MODE will use the change in brain imaging measures from the study baseline to study endpoint as the primary study outcome, providing strong causal inference that the treatment causes the changes in brain measures and depressive symptoms observed [80]. In our prior studies using these technologies, brain measures compared with traditional clinical measures provided much more sensitive and robust markers for treatment response, because brain measures are direct reports that the treatments have on the brain, which in turn underlie the change in symptom severity. MODE will be therefore identifying the biomarkers that predict and mediate change in symptoms and other clinical outcomes in high vs low frequency of psychoanalytic therapy in severely and chronically depressed patients.

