### Power calculation

Power analyses using MRI measures from prior RCTs of medication therapy for the treatment of chronic depression [81, 82] indicated that a sample size of N = 30 participants for each of the 3 arms of the study would afford us a power of 80% to detect a moderate-to-large effect size (Cohen d = 0.5) with an α = 0.05 in each imaging modality (anatomical, task-based fMRI, resting state fMRI, and DTI).

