#### Missing data

We will model missing responses/covariates in our longitudinal models. We will consider missing data mechanisms, including missing completely at random, missing at random, or missing not at random, to handle missing data due to a missed assessment time point, study dropout, or unusable MRIs. The full information maximum likelihood estimation (FIML) method will be used in fitting statistical models including LMM and LVM, which allow incomplete data (i.e., cases with missing data will contribute to the analysis).

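### With two scans, the primary treatment-by-time test is in effect a change-score comparison: valid, but less precise than a baseline-adjusted comparison using scans already planned

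*Protocol article*

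**What the plan says.** The Objectives section of the protocol article names "the change in brain imaging measures from the study baseline to study endpoint as the primary study outcome". The Data analysis section describes the primary test as "assessing a treatment-by-time interaction in multiple general linear models with repeated measures analyses in an intent-to-treat analysis". As to who enters that test, the section states: "We will test a priori Primary Hypotheses in the 60 depressed participants". The abstract gives the same test. Scans are taken twice, at baseline and at 1 year, and the models are to allow for the correlation between the two.

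On adjustment, Data analysis says: "Covariates will include age and sex of the participants". The baseline value of the brain measure is not named as a covariate, and nothing says that the two randomised arms share a baseline mean.

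On incomplete data, the Missing data section says: "The full information maximum likelihood estimation (FIML) method will be used in fitting statistical models including LMM and LVM". It adds that patients with missing data still contribute.

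The Power calculation section plans 30 patients in each randomised arm and 30 healthy controls, and claims "a power of 80% to detect a moderate-to-large effect size (Cohen d = 0.5) with an α = 0.05". No baseline-to-1-year correlation, standard deviation or dropout rate is stated.

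**The concern.** With two measurements per patient and free baseline means in each arm, the treatment-by-time interaction is the difference between arms in mean change. Subtracting the baseline in full is the best use of it only when rho is close to 1. At lower rho, part of what is subtracted is noise, and it goes into the treatment estimate. Because the arms are randomised, their true baseline means are equal, and a model that uses this fact estimates the same effect more precisely.

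This matters because there are only 30 patients per arm, and the Objectives section justifies imaging endpoints by arguing that noisy outcomes cost power. A chance baseline difference also moves a change-score estimate. The standard error of such a difference at 30 per arm is sqrt(2/30) = 0.26 SD. If a difference of that size occurred with rho 0.5, the estimate would shift by (1 - 0.5) x 0.26 = 0.13 SD, about a quarter of the 0.5 SD effect used for sample size. Such shifts average to zero over randomisations, and baseline adjustment removes them from the trial actually run.

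**Working it through.** **Inputs.** From the article: 30 patients per randomised arm, two scans, Cohen d = 0.5, alpha 0.05, claimed power 80%. Assumed: a two-sided test, equal variance at both visits, and rho over a range.

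**The plan's own figure.** A two-sample t-test with 30 per arm and d = 0.5 has 48% power; 80% would need 63 per arm (normal approximation). A change-score test reaches 80% only if d is in raw (cross-sectional) SDs and rho is about 0.77: the SD of change is then sqrt(2 x 0.23) = 0.68, and 0.5/0.68 = 0.74 SD of change, which is the difference detectable with 80% power at 30 per arm. The article does not say which unit d is in.

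**Equivalence.** A mixed model with arm, time, their interaction, and age and sex as main effects was fitted to one simulated complete data set of 60 patients. The interaction estimate was 0.468 with t = 1.6726. The two-sample t-test on change gave the same two figures.

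**Variance.** In units of the cross-sectional variance, and up to the common factor 2/n:

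- change score: 2(1 - rho)
- baseline-adjusted: 1 - rho² = (1 - rho)(1 + rho)
- ratio, adjusted over change: (1 + rho)/2, so the reduction is (1 - rho)/2

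Estimating the slope at 30 per arm multiplies the adjusted variance by about 1 + 1/55 = 1.018. At rho 0.5, for example, 0.75 x 1.018 = 0.764, a reduction of 24% instead of 25%.

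| rho | change | adjusted | reduction, large sample | reduction, 30 per arm | power, d = 0.5 raw SD | power, d = 0.5 SD of change |
|---|---|---|---|---|---|---|
| 0.4 | 1.20 | 0.84 | 30% | 29% | 41% to 54% | 48% to 62% |
| 0.5 | 1.00 | 0.75 | 25% | 24% | 48% to 59% | 48% to 59% |
| 0.7 | 0.60 | 0.51 | 15% | 13.5% | 69% to 75% | 48% to 53% |
| 0.77 | 0.46 | 0.41 | 11.5% | 10% | 80% to 84% | 48% to 52% |
| 0.8 | 0.40 | 0.36 | 10% | 8% | 85% to 88% | 48% to 51% |
| 0.9 | 0.20 | 0.19 | 5% | 3% | 99% to 99% | 48% to 49% |

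Power is for a single test at alpha 0.05, before any correction for multiple comparisons.

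**Check by simulation.** With 20,000 simulated trials per value at 30 per arm, the variance reduction was 28% at rho 0.4, 24% at 0.5, 10% at 0.77 and 3% at 0.9.

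**The case against.** The strongest reply is that nothing here is wrong. The planned test is valid and unbiased under randomisation, it matches the declared outcome of change, and the hypotheses speak of greater change. A common-baseline constraint could be left to a full analysis plan. All of this stands, so the point concerns precision and not error. It is still worth making, because the article does fix the contrast and name the covariates, and a better contrast for the same effect is available. If the full plan already sets a common baseline mean, the point is met.

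Three stronger readings are tempting, and the article does not support them.

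- A reader might infer that a repeated-measures general linear model drops patients without a 1-year scan, against intent-to-treat. The Missing data section plans full-information maximum likelihood and mixed models in which incomplete cases count, and Data analysis itself allows maximum likelihood estimates.
- A reader might infer that age and sex cannot affect the primary contrast. That holds if they enter a mixed model as main effects only. A classical repeated-measures general linear model crosses between-patient covariates with time, so they do adjust the interaction. The article does not say which form is meant.
- A reader might take 30% as the size of the loss. That is only the value at rho 0.4. The article gives no rho, and at 0.9 the gain is 3% to 5%.

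**Conclusion.** The point holds as an efficiency improvement. As described, the primary test is in effect a comparison of change scores, and adjustment for the baseline scan would estimate the same treatment effect with variance lower by (1 - rho)/2 in large samples. At 30 per arm the net gain runs from about 29% at rho 0.4 to about 3% at rho 0.9.

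The size cannot be fixed from the article. Rho is unstated and is likely to differ between cortical thickness, task activation, resting-state connectivity and diffusion measures, and from place to place in the brain. If the claimed 80% power is read as a change-score test with d in raw SDs, the implied rho is about 0.77 and the gain is 10% to 12%.

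The figures assume equal variance at both visits, complete data and randomised arms. The direction does not depend on equal variances: with SDs s0 at baseline and s1 at 1 year, the change-score variance exceeds the adjusted variance by (s0 - rho x s1)², which is never negative. The conclusion does not extend to patients against healthy controls, who are not randomised and whose baseline means are expected to differ.

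**What to change.** For the randomised high versus low frequency comparison, state the primary model as a likelihood-based longitudinal mixed model on both scans, with:

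- one common baseline mean for the two arms;
- age and sex entered with their interactions with time;
- the arm difference at 1 year as the primary estimate.

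With a common baseline this difference is also the difference in mean change, so the hypotheses need no rewording. The model keeps patients with only one usable scan, in line with the Missing data section. Plain analysis of covariance on the 1-year value should not be the primary model, since it would drop patients without a 1-year scan and so cut across that section. Comparisons with healthy controls should keep separate baseline means.

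The cost is a change of wording in the analysis plan and about one degree of freedom per model, or about 2% of variance at 30 per arm. No extra patients, scans or visits are needed. Any statement of the expected gain should give the formula and the rho assumed for each modality.

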#### Healthy control participants

Inclusion criteria are: (1) no history of prior or current psychiatric diagnoses (Structured Clinical Interview for DSM-SCID); (2) no prior history of trauma on any of the CTQ subscales; (3) 21–60 years of age; and (4) sufficient knowledge of the local language to undergo assessments. Exclusion criteria are: (1) serious physical illness; and (2) any current psychotherapeutic or psychotropic treatment. Healthy controls will be group-matched on age and gender to participants in the treatment groups (Table 2).

**Table 2 Tab2:** Inclusion and exclusion criteria for healthy participants

Inclusion Criteria	Exclusion Criteria
• No history of prior or current psychiatric diagnoses (based on Structural Clinical Interview-SCID) • CTQ: No prior history of trauma on any of the subscales • Age: 21–60 years • Sufficient knowledge of local language • Informed consent to study protocol	• Serious physical illness that strongly affects the depression or is causal for the depression • Concurrent psychotherapy • Technical exclusion criteria for MRI (metallic tattoos, pacemakers, or other metal parts in the body etc., according to special guidelines of the local MRI team)

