##### MRI Scanning

All scans will be acquired on 3.0 T scanners: Siemens Prisma (Frankfurt, Lausanne), Philips Achieva (CHLA). Signal-to-noise and contrast-to-noise was determined to be comparable across all scanning platforms (Tables 4, 5, 6 and 7).

**Table 4 Tab4:** Anatomical MRI

Scan Parameters for 3.0T MRI Scanners	Siemens	Philips
Coil	64	32
Sequence	MPRAGE	3D Gradient Echo Turbo Field Echo factor = 130
Scan plane	Sagittal	Sagittal
Direction of frequency coding	H-F	S/I
Echo time	2.75 ms	2.8 ms
Inversion Preparation Time	920 ms	920 ms
Flip Angle	9	9
Bandwidth	190 Hz/pixel	206 Hz/pixel
Repetition time (or MPRAGE TR)	2000 ms	3000 ms
Field of View	256 mm	256 mm
Matrix	256 × 256	256 × 256
Slice thickness	1.0 mm 176 slices	1.0 mm 176 slices
Phase Field of View	1.0	1.0
Number of excitations	2	2
Time	9 min, 20 secs	9 min, 3 secs

**Table 5 Tab5:** Task-based fMRI: cyberball

Sequence	2D Gradient Echoplanar	2D Gradient Echoplanar
Scan plane	Axial Oblique, parallel to the AC-PC line	Axial Oblique, parallel to the AC-PC line
Effective Echo time	34 ms	34 ms
Flip Angle	90^o^	90^o^
Repetition time	4630 ms	4630 ms
Field of View	24 cm	24 cm
Matrix	112 × 112	112 × 112
Slice thickness	2.4 mm	2.4 mm
Number of Volumes/Run	215	137
In-Plane Resolution	24 cm/112 × 24 cm/112 = 2.14 × 2.14 mm2	24 cm/112 × 24 cm/112 = 2.14 × 2.14 mm2
Number of Slices	60	60
Number of Runs	1	1
Time	16 min 40 s (1000 s)	10 min 34 s (643 s)

**Table 6 Tab6:** Resting-State fMRI

	**Siemens**	**Philips**
Sequence	2D Gradient Echoplanar	2D Gradient Echoplanar
Scan plane	Axial Oblique, parallel to the AC-PC line	Axial Oblique, parallel to the AC-PC line
Echo time	34 ms	34 ms
Flip Angle	90^o^	90^o^
Repetition time	4630 ms	4630 ms
Field of View	24 cm	24 cm
Matrix	112 × 112	112 × 112
Slice thickness	2.4 mm	2.4 mm
Number of Volumes/Run	90	90
In-Plane Resolution	24 cm/112 × 24 cm/112 = 2.14 × 2.14 mm2	24 cm/112 × 24 cm/112 = 2.14 × 2.14 mm2
Number of Slices	60	60
Number of Runs	1	1
Time	7 min 11 s (1000 s)	7 min 11 s (1000 s)

**Table 7 Tab7:** Diffusion tensor imaging

	**Siemens**	**Philips**
Sequence	2D Gradient Echoplanar	2D, single-shot, echo-planar imaging
Scan plane	Axial Oblique, parallel to the AC-PC line	Axial Oblique, parallel to the AC-PC line
Echo time	66 ms	66 ms
Flip Angle	90^o^	90^o^
Repetition time	7300 ms	7700 ms
Field of View	24 cm	24 cm
Matrix	112 × 112	112 × 112
Slice thickness	2.0 mm	2.0 mm
Acceleration factor	2 (GRAPPA)	2 (ASSET)
Number of DWIs	64	64

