## Procedures

### Data collection sites

Recruitment and treatment sites will be located in one center in the US (Los Angeles) and six centers in Europe (Germany: Frankfurt a.M., Cologne, Leipzig, Giessen, Mainz; and Switzerland: Lausanne). MRI scanning occurs in Los Angeles, Frankfurt a.M., and Lausanne. MRI data are processed in Los Angeles (CHLA). A clinical agreement has been signed and approved by each participating site.

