### Randomization

The randomization procedure will consist of a computer-generated sequence of random numbers using SPSS (SPSS Statistics, version 28), which will then be used to allocate patients to either of the 2 treatment arms. The randomization sequence will be generated and maintained by an independent study administrator in Frankfurt. Once the patient is included the ID number is communicated to the study administration in Frankfurt. On the same day, the randomization arm will be communicated to the local team and applied to the participant included.

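### Scanner is absent from the named covariates and from control matching, although three scanners of two vendors are used and the Cyberball run is 57% longer on one platform

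*Protocol article*

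**What the plan says.** The Data analysis section tests the primary hypotheses in the 60 patients through a treatment-by-time interaction. On adjustment it says: "Covariates will include age and sex of the participants". No scanner or site term and no harmonisation step is mentioned anywhere in the article.

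On equipment, the Data collection sites section says: "MRI scanning occurs in Los Angeles, Frankfurt a.M., and Lausanne". The MRI Scanning section names a Siemens Prisma in Frankfurt and in Lausanne and a Philips Achieva in Los Angeles, and reports that signal-to-noise and contrast-to-noise were comparable. Tables 4 to 7 then list acquisition settings that differ by vendor. The largest difference is in Cyberball (Table 5): 215 against 137 volumes per run.

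On controls: "Healthy controls will be group-matched on age and gender to participants in the treatment groups". The Data analysis section makes these 30 people the reference for deciding whether a brain measure has normalised. The Brain structure hypothesis requires patients at one year to be statistically indistinguishable from them.

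On allocation, the Randomization section describes a "computer-generated sequence of random numbers using SPSS", held centrally.

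**The concern.** The article fixes a model and publishes acquisition tables showing that the primary outcomes are not measured identically at all sites. Scanner is therefore a plausible source of variation that the stated model does not handle, although it is known for every participant.

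Two comparisons are at stake, and they are exposed differently.

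- **High versus low frequency.** This is a randomised comparison of within-patient change. Scanner can cost precision, and it can leave a chance imbalance if change over the year differs by scanner.
- **Patients versus controls.** This is not randomised, and the controls are not described as matched on scanner. A difference in scanner mix can look like abnormality at baseline, or like normalisation at one year. Unmodelled scanner variance also widens the spread, which makes it easier to find no difference from controls.

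Cyberball raises a further point. The task has inclusion, exclusion and re-inclusion phases, and the article does not say how they fit two runs of such different length.

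**Working it through.** **Inputs from the article**
- Cyberball: 215 and 137 volumes, repetition time 4630 ms in both columns (Table 5). The table as shown has no header row, so Siemens first and Philips second is inferred from the neighbouring tables.
- Arms of 30 and 30 patients, and 30 controls (Study design).
- Design effect d = 0.5 (Power calculation).

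**Inputs assumed, because the article does not give them**
- Patients per scanner, the difference in scanner mix between groups, and the size of a scanner offset.

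**1. Cyberball run length = volumes × repetition time**
- 215 × 4.63 s = 995.5 s (printed: 16 min 40 s = 1000 s).
- 137 × 4.63 s = 634.3 s (printed: 10 min 34 s = 634 s).
- Ratio 215 / 137 = 1.57, so one run is 57% longer.

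**2. Precision of one person's Cyberball estimate**
- With equal noise per volume (assumed), the within-run sampling variance on the shorter run is 1.57 times that on the longer run, and the standard error is √1.57 = 1.25 times as large.
- This is within-run variance only. Group comparisons also contain between-person variance, so the effect on the arm contrast is smaller.

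**3. Other differences between the vendor columns**
- Coil 64 against 32 and anatomical repetition time 2000 against 3000 ms (Table 4).
- DTI repetition time 7300 against 7700 ms (Table 7).

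**4. Chance imbalance between the randomised arms**
- With m of the 60 patients on one scanner and arms of 30 each, the number X of those patients in one arm is hypergeometric: P(X = k) = C(m, k) × C(60 − m, 30 − k) / C(60, 30).
- For m = 20, P(X ≤ 7 or X ≥ 13) = 0.17. A 13:7 split means 13/30 − 7/30 = 20 percentage points.
- For m = 10, 15 and 30, the chance of a difference of at least 20 points is 8%, 7% and 20%.
- The resulting error in the arm contrast is the share difference times the difference between scanners in mean change. A constant offset contributes nothing to that when both scans of a patient come from the same machine.

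**5. Patient-control comparison**
- Shift = difference in scanner mix × scanner offset. With 20 points and 0.5 to 1 SD: 0.20 × 0.5 = 0.1 SD, and 0.20 × 1 = 0.2 SD.
- Inflation of the cross-sectional SD with a share q on one scanner and offset δ is √(1 + q(1 − q)δ²). For q = 1/3, δ = 0.5 gives 1.03 and δ = 1 gives 1.11, so 3% to 11%.

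**6. Printed times (clerical)**
- Table 5, second column: 10 min 34 s is 634 s and agrees with the volumes, but the bracket prints 643 s.
- Table 6, both columns: 90 × 4.63 s = 416.7 s, while 7 min 11 s is 431 s and the bracket prints 1000 s.

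**The case against.** The strongest reply is that the article names two covariates without saying that there are no others. It condenses a fuller protocol, and scanner terms or harmonisation may sit in an analysis plan or imaging manual that is not shown. That stands against any claim that scanner is definitely excluded. The point here is narrower: the named set can be improved at almost no cost, and nothing else in the article compensates.

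A second reply is that the primary test compares within-patient changes between randomised arms. This largely stands. A reader might infer that scanner differences bias the primary test, and the documents do not support that. A constant offset cancels for patients with both scans on one machine, and randomisation turns any scanner-by-time effect into chance imbalance. Two limits apply. The article does not say that each patient returns to the same scanner. Its likelihood-based handling of missing data also lets patients with a single scan contribute, and for them an offset does not fully cancel.

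A third reply is the statement that signal-to-noise and contrast-to-noise are comparable. It does not answer the point: such comparability neither equalises run length nor removes offsets in thickness, diffusion or activation.

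Three further inferences are tempting but unsupported:
- That scanner is the dominant source of variation. No section quantifies it.
- That randomisation is unstratified. The article is only silent on this.
- That participants meet a different task at different sites. The article describes one task with three phases and gives no phase lengths.

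**Conclusion.** The concern holds in a limited form. Age and sex are the only covariates named, age and gender the only matching factors, and acquisition differs by vendor. The 57% difference in Cyberball run length follows from the printed volumes and repetition time. It depends on no assumption except the inferred column order, which affects only which platform has the longer run.

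For the arm contrast, the harm is lost precision, unequal error variance and a chance imbalance that matters only if change differs by scanner. The probability of a 20-point imbalance is about 17% under the assumed 20 patients on one scanner, and 7% to 20% over the other numbers tried.

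For the patient-control comparison, the harm is bias. The illustrative 0.1 to 0.2 SD is not negligible beside a design effect of 0.5, but it multiplies two assumed figures. It shows what is possible, not what will occur.

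The errors in the printed times are clerical and do not affect the models. The change should be made, but the randomised comparison is not invalid without it.

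**What to change.** - **Primary models.** Add scanner (three levels) and scanner-by-time. For patients with both scans on one machine, scanner-by-time is the term that protects the arm contrast. The main effect matters for single-scan patients. Say whether each participant is rescanned on the same machine.
- **Patient-control comparisons.** Include scanner in every one, and match the remaining controls within scanner where feasible.
- **Cyberball.** State the length of each phase on each platform. Use comparable phases, or weight for unequal precision. Keep a matched-volume analysis as a sensitivity check, because trimming could discard up to 215 − 137 = 78 of 215 volumes (36%) on the longer run.
- **Tables 5 and 6.** Reconcile the printed times with the volumes and repetition time.
- **Optional.** Stratify any remaining randomisation by scanner.

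Cost: two degrees of freedom for scanner and two for scanner-by-time, plus some added analysis work. Matching controls within scanner may slow their recruitment.

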#### Primary outcomes: MRI brain measures

Assessment will comprise the following MRI brain measures. Anatomical MRI: measures of cortical thickness at all points across the cerebrum. Resting State Functional MRI (rsfMRI): measures of functional connectivity throughout the brain. Cyberball Task-Related Functional MRI (fMRI): measures of brain activation throughout the brain in response to trust, mistrust (social exclusion), and rebuilding of trust (social re-inclusion). Diffusion Tensor Imaging (DTI): measures of fractional anisotropy and average diffusion coefficient.

What these outcomes tell us about the brain MRI is an entirely safe way of imaging the brain at any age. It is routinely performed in unsedated people at multiple time points, including multiple time points within an RCT, and without the need for exposure to any radioactivity. MRI scanning can be performed in different modes, with each modality providing unique information probing different aspects of the brain’s structural and functional organization. *Anatomical MRI* provides information about brain structure, most commonly the volumes and shapes of particular brain regions. *Diffusion Tensor Imaging (DTI)* provides information about tissue organization within the brain, especially white matter fibers that connect one brain region to another. At each voxel, Fractional Anisotropy (FA) measures the directional diffusion of water, Mean Diffusivity (MD) measures the overall diffusion of water, Axial Diffusivity (AD) measures diffusion along the long axis of diffusion, which is presumed to be along the long axis of the fiber bundle, and Radial Diffusivity (RD) measures diffusion perpendicular to the long axis of diffusion or fiber bundle. *Functional MRI (fMRI)* provides measures of time-dependent changes in the relative concentration of deoxyhemoglobin within each voxel, which itself is driven largely by changes in oxygen use and the underlying changes in neuronal activity within the voxel [87, 88]. Measures of *resting state connectivity (rsfMRI)* are in essence measures of cross-correlation for the fMRI series of two different voxels (i.e., two different points in the brain), which assesses how strongly those two regions communicate with one another over time.

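### The plan says FDR correction maintains study-wide Type I error, but FDR does not control that error rate, whichever family of tests it is applied to

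*Protocol article*

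**What the plan says.** The Data analysis section makes an explicit error-rate claim for the primary hypotheses: "We will ensure that overall, study-wide Type I error-rate is maintained, correcting for multiple comparisons using False Discovery Rate (FDR"). The same paragraph sets the display threshold: FDR-corrected p-"values < 0.05 will be color-coded and displayed on a template brain".

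The primary hypotheses are tested by "assessing a treatment-by-time interaction in multiple general linear models with repeated measures analyses", with several dependent variables, "including cortical thickness, task-based fMRI activation, resting state connectivity, and FA & ADC measures". That is at least five measures. The primary outcomes are whole-brain. For anatomy, for example, they are "measures of cortical thickness at all points across the cerebrum".

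The Power calculation section sets the sample size "with an α = 0.05 in each imaging modality (anatomical, task-based fMRI, resting state fMRI, and DTI"), which is four modalities at 5% each. On dependence, the Data analysis section refers to "the spatial correlation within each of our imaging measures" and to correlation between the two time points. It says nothing about dependence between measures.

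The article does not say whether FDR is applied within each map, within each modality or once over everything. It names no single primary measure, no order of testing and no split of alpha across modalities.

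**The concern.** FDR and Type I error over a set of tests are different quantities. FDR is the expected proportion of false rejections among all rejections. Study-wide Type I error is the probability of at least one false rejection. They coincide only when no effect exists anywhere in the family, because then every rejection is false. Once some effects are real, FDR allows false findings roughly in proportion to the true ones. A statement that FDR maintains study-wide Type I error is therefore wrong in general, and no further detail about FDR alone can make it right.

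These maps are the primary outcomes, and there is one primary hypothesis per modality under a single heading claim of normalisation. If a significant region appears in one modality only, the sentence would let the authors present it as protected by a study-wide guarantee. The article also intends to use identified mediators as surrogate endpoints in later trials, so a region reported under that guarantee could be carried forward.

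**Working it through.** **The plan's own figure.** No study-wide number is printed. The implied one is 0.05, from the FDR threshold. Whether it can be reproduced depends on the family, so both readings are worked through.

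**Inputs from the article.** FDR threshold 0.05; four modalities (Power calculation); at least five measures (Data analysis: thickness, task activation, resting connectivity, FA, ADC).

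**Inputs assumed.** Benjamini-Hochberg procedure; 200 points per map in the simulations; correlations and effect sizes as stated below. The article gives none of these.

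**Reading 1: FDR run separately in each modality or measure, no effect anywhere.** Within each family, FDR at 0.05 then equals a 5% chance of any rejection when points are independent. For k independent families the chance of at least one false-positive map is 1 − 0.95^k:

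- k = 4: 1 − 0.95^4 = 18.5% (simulated 19.2%)
- k = 5: 1 − 0.95^5 = 22.6% (simulated 22.9%)

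Positive correlation lowers this. With an assumed correlation of 0.5 between points within a map, and correlation of the shared part across maps varied from 0 to 0.9, the simulated chance was about 8% to 12% for four maps and 8% to 14% for five.

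**Reading 2: one FDR over all maps pooled, no effect anywhere.** Simulated chance of any false rejection: 5.3% (four maps) and 5.2% (five maps) under independence, and 2.6% to 3.8% with the correlations above. In this scenario the nominal 5% is met.

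**Reading 2 with a real effect in one of five maps.** Assume a z shift of 3.5 in a fraction of that map's 200 points, with the other four maps (800 points) truly null and all points independent. Benjamini-Hochberg rejects p-values up to t = 0.05 × (number rejected) / 1000, so true rejections in one map raise t for every map.

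- Effect in 100% of the map (200 points): about 168 rejections are expected, so t ≈ 0.05 × 168 / 1000 = 0.0084. Expected false points in the null maps: 800 × 0.0084 = 6.7. Chance of at least one: 1 − (1 − 0.0084)^800 ≈ 99.9%. Simulated: over 99%.
- Effect in 20% (40 points): about 25.6 rejections, t ≈ 0.05 × 25.6 / 1000 = 0.00128. Chance of at least one: 1 − (1 − 0.00128)^800 ≈ 64%. Simulated: 64%.
- Effect in 5% (10 points): the count rejected is too small and variable for this approximation. Simulated: about 20% to 21%.

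Throughout, the realised FDR stayed at about 4% to 5%. The procedure does what it is designed to do, but it does not hold the chance of a false claim at 5%.

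**If a study-wide claim is to be kept.** With the printed inputs (30 per arm, d = 0.5, two-sided assumed), the noncentrality is 0.5 × √(30/2) = 1.936. Power for a single comparison is Φ(1.936 − 1.960) = 49% at alpha 0.05, and Φ(1.936 − 2.498) = 29% at the first Holm step for four modalities, 0.05/4 = 0.0125.

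**The case against.** A reader might infer that the study as planned carries a 19% to 23% chance of a false-positive map. The documents do not support that as a flat statement. The figure needs FDR to be run separately per modality or measure, and it needs independent maps. The article states neither. The words about study-wide control read at least as naturally as one pooled family, which meets about 5% when nothing is real. All maps come from the same 60 patients, and FA and ADC come from the same diffusion scan, so independence is doubtful. The alpha of 0.05 per modality is a sample-size input and not a testing rule. This objection stands, and the figure can be given only as an upper value with its conditions.

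A reader might also infer that any isolated false point could be reported as confirming normalisation. That goes too far. The hypotheses ask for more than a significant point. Thickness must start abnormal, change more under high frequency, be indistinguishable from controls at one year and track clinical improvement. Activation names ventral medial regions, connectivity points to the default mode network, and the diffusion hypothesis fixes directions. These conditions reduce the scope for a stray finding to pass as confirmation, although they do not create study-wide error control.

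Finally, FDR is a legitimate method for whole-brain maps, and the choice of family, alpha allocation and regional summaries is commonly left to a statistical analysis plan, which is not shown. That is fair, and the absence of those details is not the fault found here. The fault is a sentence that is present and attributes to FDR a property it lacks.

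**Conclusion.** The sentence is wrong as written: FDR does not give strong control of study-wide Type I error. This conclusion needs no assumption about the family, because neither reading gives that control.

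- Separate families: up to 18.5% (four modalities) or 22.6% (five measures) with no effect anywhere if maps are independent; about 8% to 14% under the assumed positive correlations.
- One pooled family: about 5% with no effect anywhere, but not controlled once one modality has a real effect. The chance of a false point in a null map is then about 20% to over 99%, for an assumed z shift of 3.5 in 5% to 100% of one map's points.

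The first conclusion is certain; the sizes are conditional on the assumptions shown. The defect concerns what may be claimed for the primary outcomes. It does not show that the mapping analysis itself is unsound.

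**What to change.** Before the maps are analysed, name the family to which FDR is applied (each map, each modality, or all maps together), and replace the study-wide Type I error claim with a description such as: *FDR controlled at 0.05 within [named family]*. This is a change of wording. It needs no new data or analysis and costs no power. It should be settled before the maps are seen, because choosing the family afterwards would itself introduce bias.

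Only if the sponsor wishes to keep a study-wide claim, add a family-wise procedure across the four modalities, for example Holm on one prespecified summary measure per modality, with the whole-brain maps reported as secondary. The activation and connectivity hypotheses already point to candidate targets; thickness and diffusion would need a summary to be chosen. This is a real change to the primary analysis. The first step would be tested at 0.0125, where power for a single comparison at d = 0.5 with 30 per arm falls from about 49% to about 29%. Whether a well-chosen summary would offset that loss cannot be judged from the article.
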